### Procedures

The development of SOS Dating comprised eight steps: needs evaluation, definition of the intervention’s objective, construction of the customization questionnaire, elaboration of the message library, entering the content into the customization software, intervention pre-test, and evaluation planning [47].

#### Step 1: Needs evaluation

The needs evaluation consisted of three empirical studies with youths, both victims and not of dating violence, to identify relevant objectives for the intervention and develop its content.

The first study had the purpose to examine the psychosocial determinants of dating violence and was conducted with seven focus groups of adolescents (*n* = 12) coming from public and private schools and young students (*n* = 16) from private and public universities. The focus groups explored the psychosocial determinants of dating violence, as recommended by the I-Change Model, and were conducted separately according to gender and school/university. The data, examined by deductive thematic analysis, was categorized as knowledge, social norms, social support, models, attitudes, self-efficacy, action plans, and suggestions for preventive initiatives against dating violence. The results pointed to gaps in the knowledge of the psychological and material manifestations of dating violence, with physical and sexual being the most acknowledged forms. Similarly, ignorance of non-violent conflict resolution among students was apparent, as well as what positive and healthy aspects of romantic relationships would entail. Dating violence was reported as acceptable in several situations, such as in the case of betrayal, when attacked first, and if one or both partners are intoxicated. Pro-violence social norms attached to sexist stereotypes were commonly reported. The participants reported financial dependence and having kids as conditions that can promote submission to violence and inhibit social support for leaving the abusive relationship. Finally, they reported action plans with potentially negative impacts, such as resigning themselves to violence, acting indifferently to the partner, and responding to violence with violence, but there were some positive plans as well, such as terminating the relationship or looking for professional help. The participants suggested that preventive interventions might develop critical thinking about gender stereotypes and foster respect for the partner’s individuality.

The second study investigated the characteristics, triggers and consequences of violent conflicts in dating relationships. It was conducted via individual interviews with ten participants, six men and four women, aged 17 to 27, who had experienced dating violence, either as victims or as perpetrator-victims (i.e. bidirectional violence). The results were analyzed using deductive thematic analysis. The participants described their relationships as a mix of positive and negative experiences, with strong affective involvement but with the use of ineffective strategies of conflict management. Among those, resignation to the partner’s impositions was reported; threats, possessiveness, and casting blame to control the other’s behavior; poor emotional control (cursing and bouts of rage) accompanied by psychological, physical, and mental aggressions; attempts at reconciliation and repairing; and the withdrawal into silence and indifference toward the partner. It was reported that all these strategies resulted in new conflicts and subsequent future violence, causing great suffering to the parties involved. Furthermore, data indicated the hyperactivation of the system of attachment in the face of signals interpreted as abandonment by the partner, for example silence and distancing accompanied by anxious responses, such as emotional outbursts to make the other listen.

The third study, aimed to examine emotional intimacy and safety in the romantic relationship, keeping attachment theory as the theoretical lens. It used semi-structured individual interviews with youths between sixteen and twenty-three years of age who had dating experience. The results revealed variability among the interviewees regarding the intimacy experience, with higher levels of intimacy being connected to the exchange of social support between partners and sensitivity to each other’s needs, and threatening levels of intimacy connected to evasiveness when seeking support from the partner and negative conflict resolution strategies. The data aligned with the recommendations of attachment theory, which are that partner’s availability and accessibility are the central path for promoting emotional closeness in romantic relationships.

In short, the needs evaluation demonstrated the urgency of the intervention, taking into account its main findings: violence is seen as natural in romantic relationships; gender stereotypes justifies attitudes of acceptance of violence; negative social modeling for romantic relationships are largely present in closer relationships; psychological and material violence are barely recognized as violence; betrayal is the most difficult situation to not using violence against the partner; there are negative strategies to cope with conflicts, including submission, emotional dysregulation and withdrawal; and violent conflicts are related to non responsive and hostile partners’ answers.

#### Step 2: Defining the target group and intervention objectives

The data collected from all three needs evaluation studies underpinned the elaboration of the intervention’s objectives (Table 1) and target group. The target group selected for the intervention was youths (15–29 years old) who had a romantic partner. The results of needs assessment suggested that the intervention should (a) prescribe objectives to address psychosocial determinants of dating violence which were also in line with socio-cognitive ecological models such as the I-Change Model, (b) address not only violence but relationship quality too, focusing on the partners’ mechanisms of availability and accessibility to strengthen emotional closeness, as informed by attachment theory, (c) discuss gender stereotypes and how they are connected to attitudes and social norms that sustain violence, (d) consider attachment styles and their impacts on emotional regulation as a barrier to self-efficacy for coping with conflict and breaking the connection with the partner, and (e) consider contextual diversity in action plans, ranging from daily interactions, to conflict situations as well as currently being in a violent situation.

#### Step 3: Construction of questionnaire for tailoring

In order to address the various objectives to be addressed in a computer tailored intervention, questionnaire based on the I-Change Model was developed, titled the Dating Violence Determinant Questionnaire. The instrument considers several determinants predicted in the I-Change Model: awareness (eight items, for instance, “Conflict can occur in a relationship without there being violence”); attitudes (six items, for example, “When you depend on the partner’s money to live, it’s better to endure the violence”); social norms (nine items, for instance, “Someone who cheats deserves to be attacked”); models (two items, for example, “Of the people you know, who has a romantic relationship (dating or marriage) that is positive, with companionship, respect, and affection? You can choose more than one option: parents, aunts and uncles, grandparents, friends, neighbors, nobody”); social support (one item, “Who would you ask for help to get out of a violent relationship? You can choose more than one option: father, mother, siblings, friends, church group, police, nobody”); self-efficacy (eight items, for example, “How hard would it be for you to ‘keep cool’ and not be violent towards your partner if he or she had lied to you”); and action plans, subdivided into action plans to help in daily life with the partner (six items, for instance, “If I was down, I would tell him/her my problems and ask for help”), dealing with conflicts (14 items, for instance, “I’d get my revenge, I’d get back at him/her”), and protecting against violence (seven items, for example, “I would end the relationship”).

We have chosen a closed question format with multiple choice answers for the following determinants: awareness, social support and action plans. A Likert scale was used to evaluate the determinants: attitude (4 points, from disagree completely to agree completely), social norms (5 points, from almost everyone to almost no one), and self-efficacy (4 points, from very easy to very difficult). The instrument was submitted to semantic validation; confusing terms or those with double meanings were corrected.

#### Step 4: Elaboration of the message library

Once the intervention objectives had been established and the Dating Violence Determinant Questionnaire had been created, the elaboration of a repository of advice messages was started, resulting in a message library. The message library was developed according to recommendations of Kreuter et al. [47]. First, tables were built for each determinant predicted in the I-Change Model (awareness, attitudes, social support, social norms, models, self-efficacy, and positive and negative action plans) with the message title (for identification purposes), objective (changes targeted by that message), origin (which items in the questionnaire supplied the data that is the basis of that message), format (didactic resource for message expression, such as narration, vignette, comparative table, video, etc.), theory and base evidence (studies that support the message’s content), main problem (principal presumed life context of user), tone (emotional aspect of the message, i.e., empathetic or informative), concepts (message content), and message (the guidance itself).

After this systematic planning, the messages were elaborated by psychology students, who were told to write freely, as if they were giving advice to a friend. This strategy was adopted to maximize the accessibility and friendly tone of the messages. Next, the messages were reviewed by researchers with expertise in the research subject. At this stage, it was verified that the elaborated guidance covered the objectives and concepts expected of it.

This process resulted in 67 messages. In session 1, four variations were created based on attachment style and eight based on the status of violence in the current relationship. In session 2, eleven messages were elaborated regarding awareness of dating violence, six about violent relationship models, six about non-violent relationship models, and lastly four action plans were created to cover daily life with the partner. In session 3, six message variations were developed about social norms, three on self-efficacy, and four of action plans for conflict management. Finally, in session 4, six messages were composed concerning attitudes, six about social support, and three for action plans to deal with dating violence. Table 1 shows the objectives of each session and the customization variables by session.

The messages consist of a combination of text segments, with the presence and position of each in the presented message body determined by the participant’s answers. The answers to the items are used as input, generating a final classification of attachment style. This classification becomes the variable responsible for determining which segments are used in the message subsequently presented to the participant. Moreover, it is possible to use this previously calculated variable as input for the succeeding questionnaires.

Care was taken that the combination of various messages would result in coherent texts. The text segments were constant only within a specific set of classifications, serving as introductory, connecting, or concluding passages, whereas the remaining part was tailored based on the response of the participant to the question.

The Portuguese language requires special attention to grammatical gender. To write a text that seems reader-directed, it is necessary to use the correct gender for the participant and partner. Since gender use occurs according to well-defined rules, it was possible to adapt the text for several possibilities.

#### Step 5: Entering the content into the software for tailoring

In parallel with the previous step, the intervention’s webpage and its visual identity were developed. After finishing the message library, all instruments were entered into *TailorBuilder*, which then customized the guidance to the participants’ profiles. This stage involved the employment of a programmer and a UX (user experience) expert to conceive and implement the interaction with the SOS Dating participants.

#### Step 6: Intervention pre-testing

Next, the intervention’s pre-testing was performed. Three pre-testing sessions were held, the first with three young people potential users, the second with three professionals working at centers for victims of domestic violence, and the third with twenty university students. The main findings of pre-testing were related to the format and content:
The young people potential users thought the messages were too long and that SOS Dating’s interface was not clear;The professionals noted a risk for side-effects in the guidance regarding the bidirectional violence and conflict management for participants whose relationships were already violent.All participants reported perceiving the intervention as relevant.Responding to these findings, an extensive review was performed of the intervention’s visual aspects and content.A new visual identity, aiming for greater interface elements clarity, was proposed and content readability was improved.The messages were shortened to reduce the cognitive demand on the participants;Tailoring adjustments were made in conflict management and actions plans regarding the status of violence in the relationship, with the purpose of preventing iatrogenic effects and boosting participant identification with the intervention.

After these adjustments, new wave of pre-testing was done with two potential users and two experts in domestic violence, which approved the aforementioned changes.

#### Step 7: Evaluation planning

Two evaluation modes were planned, efficacy and usability.

### Efficacy evaluation

#### Objectives

The intervention was designed to reduce victimization and perpetration of physical, sexual, and psychological violence in dating (primary outcomes) and to boost the quality of the romantic relationship as well as conflict management skills and help seeking (secondary outcomes).

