#### Calculation of the sample size

The calculation of the sample size for this study uses a conservative procedure to identify a 10% reduction in dating violence prevalence on the intervention group compared to the control group. Adopting a significance level of 5%, a testing power of 80%, and a 50% dropout rate over the course of the study, it was calculated that each condition should have 610 individuals.

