#### Participants and design

An experimental design with a pre-test evaluation and three-month follow-up will be used. Youths between 15 and 29 years of age and their current partners will be invited to participate. A sample of 1220 youths, which will be randomly and evenly divided between the experimental and control groups, is expected. Participants younger than 15 and older than 29 or not currently in a dating relationship will be excluded from the intervention.

The intervention group will receive the SOS Dating intervention, while the control group will receive general information about dating violence, life skills, and sexual and reproductive rights, based on the book “Telling a night out from a trap: a Guide for the Empowerment of Teens in Intimate Relationships” (Diferenciando Baladas de Ciladas: um Guia para o Empoderamento de Adolescentes em Relacionamentos Íntimos) [48], available at http://www.geppsvida.com.br/publicacoes/cartilhas-e-guias/.

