### Statistical analysis

Descriptive statistics will be used to describe the characteristics of the participants in the baseline and usability data. The principal analyses will consist of intra- and intergroup comparisons between the baseline and the three-month follow-up on the outcomes of victimization and perpetration of physical, psychological, and sexual violence; quality of the romantic relationship; and conflict management skills. Multivariate analysis of covariance will be used to examine the efficacy of the intervention on these outcomes. The attachment style and the relationship’s violence status will be used as covariates. In addition to this, intergroup comparisons will be conducted using the *t*-test on the three-month follow-up outcome of seeking help. Moderation analysis will be employed to evaluate the differential effects of the intervention based on gender, age, and sexual orientation. A significance level of 0.05 will be adopted.

Omitted or incomplete data will be handled via multiple imputation using the Missing Value Analysis procedure of SPSS Statistics. Intention-to-treat analyses will be carried out, and all randomized participants will be posteriorly included regardless of having completed the intervention or not. The effects of Dating SOS will be estimated utilizing Cohen’s d (where values around 0.2 = small effect size; around 0.5 = medium effect size; and around 0.8 = large effect size).

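### Six co-equal primary violence outcomes have no stated success rule, and the 80% power covers one prevalence contrast at an unadjusted 5%

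*Protocol article*

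**What the plan says.** All places are in the protocol article.

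- **Objectives.** The intervention is to "reduce victimization and perpetration of physical, sexual, and psychological violence in dating (primary outcomes". That is victimization and perpetration, each for three types of violence. No outcome is ranked above another. The secondary aims are to "boost the quality of the romantic relationship as well as conflict management skills and help seeking (secondary outcomes".
- **Statistical analysis.** The principal analyses list the violence outcomes together with relationship quality and conflict management skills, and name MANCOVA as the test of efficacy on all of them. Help seeking gets a separate *t*-test, and moderation analyses follow. One level is given for everything: "A significance level of 0.05 will be adopted". The section does not say how a single violence outcome is to be read once the MANCOVA result is known, or which pattern of results counts as success.
- **Calculation of the sample size.** The target is to "identify a 10% reduction in dating violence prevalence on the intervention group", a single quantity. The remaining inputs are given as "Adopting a significance level of 5%, a testing power of 80%, and a 50% dropout rate over the course of the study", and "it was calculated that each condition should have 610 individuals".

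**The concern.** Three statements do not fit together: six co-equal primary outcomes, one undivided 0.05, and a power calculation for one contrast.

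The joint test does not close the gap. MANCOVA asks whether anything in the set differs between arms; it does not say what. The set includes relationship quality and conflict skills, which the intervention is also designed to improve. A gain in those alone can make the joint test significant. A reader who then looks at the six violence outcomes one by one has no rule to follow, and the joint test no longer protects that look.

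At stake is what may be reported as a reduction in violence. The Discussion expects a positive result to inform public policy. A claim on one of six primaries, chosen after the data are seen, would carry more than the nominal error, and the 80% does not describe the power of the primary family.

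**Working it through.** **1. Reproducing 610 per arm.** The control prevalence, whether the 10% is absolute, and the sidedness are not stated. Assume 50% v 40% with the pooled-variance formula:

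n = [z(alpha) × √(2 × p̄ × (1 − p̄)) + z(power) × √(p1(1 − p1) + p2(1 − p2))]² / (p1 − p2)², with p̄ = 0.45.

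- One-sided 5%: [1.645 × √0.495 + 0.842 × √0.49]² / 0.01 = 305. Divided by (1 − 0.50) this is 610, an exact match.
- Two-sided 5%: 388, then 776; no match.
- Two-sided with continuity correction: 408, then 816, no match; 408 × 1.5 = 612 is close. At 80% v 70% the corrected figure is 313, then 626, also close.

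Every variant found that matches or comes close uses one contrast at an undivided 5%.

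**2. Six separate two-sided tests at 0.05, no true effect.** If independent, 1 − 0.95⁶ = 26.5%. For false claims of benefit only, 1 − 0.975⁶ = 14.1%. The article gives no correlation among the six outcomes, so a common value was assumed and simulated:

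| Correlation | Any false claim | False benefit only |
|---|---|---|
| 0 | 26.5% | 14.1% |
| 0.3 | 24.1% | 12.2% |
| 0.5 | 20.7% | 10.4% |
| 0.7 | 16.5% | 8.2% |
| 0.9 | 10.9% | 5.4% |

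**3. The same six read only after a significant MANCOVA at 0.05.**

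- *Nothing changes*, six-outcome MANCOVA: any false claim in 4.9% (correlation 0) to 3.2% (0.7). The gate works here.
- *Quality improves, violence does not*: 11 scores (6 violence, 2 relationship-quality factors, 3 conflict strategies), 305 completers per arm, an assumed 0.3 SD gain on both quality factors, large-sample approximation. The gate opens in 97-100% of runs, and a false violence claim follows in 26%, 24%, 21% and 16% at correlation 0, 0.3, 0.5 and 0.7. With a 0.2 SD gain it is still 16-22%.
- *One violence outcome truly changes strongly* (5 standard errors), six-outcome MANCOVA: a false claim on one of the other five in 23% (correlation 0) to 15% (0.7).

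**4. Power per outcome at 0.05/6 = 0.00833**, the strictest Holm step, for 50% v 40% and 305 per arm. Power = Φ[(0.10 − z × se0) / se1], with se0 = √(0.495/305) = 0.0403 and se1 = √(0.49/305) = 0.0401.

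- One-sided: z moves from 1.645 to 2.394, and power from 80% to 54%.
- Two-sided: z moves from 1.960 to 2.638, and power from 70% to 44%.

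The gap between 80% and 70% comes from sidedness. Only the fall within each line is due to multiplicity.

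**The case against.** A reader might infer that the plan tests each of the six outcomes separately at 0.05 and so carries an unconditional 16-26% error. The documents do not support that. The one efficacy test named for these outcomes is MANCOVA; the 0.05 sentence is general and also covers help seeking and moderation. If univariate results are read only after a significant joint test and nothing has changed, the error stays at or below about 5%. The 16-26% is therefore conditional.

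The scenario behind it is also assumed: the article gives no effect size for relationship quality, no count of dependent variables, no correlations, and does not say that one model holds all scores. Nor does 305 per arm describe the planned analysis, which is intention-to-treat with multiple imputation; it is the completer count implied by the stated dropout. With complete data on all 610 per arm, power at 0.05/6 would be 87% one-sided or 81% two-sided. A false success means a false benefit, for which the range is about 8-14%.

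A reader might also infer that no correction will be made. The article does not say so, and rules for follow-up tests are often left to an analysis plan, which is not shown. That limits how much weight the silence can bear.

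What remains does not rest on silence. The article itself fixes six unranked primaries, places them with secondary outcomes under one test and one level, and sizes the trial on one unadjusted contrast. A correction added later would control the error but leave the printed power statement inapplicable to the family.

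**Conclusion.** The concern holds in conditional form. The plan as printed does not control false claims on single violence outcomes once some other outcome truly improves. In that case, with single outcomes read at 0.05, the chance of at least one false two-sided violence claim is about 16-26%, and of a false benefit about 8-14%, over assumed correlations from 0.7 to 0. If nothing changes and the MANCOVA acts as a gate, there is no excess.

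The 80% applies to one prevalence contrast at an unadjusted 5%. At 0.05/6 it becomes about 54% on the one-sided basis that reproduces 610; on a two-sided basis 70% becomes 44%. Both rest on an assumed 50% v 40% and 305 completers per arm. They are powers for two proportions, the quantity used in the sample size, not for the MANCOVA.

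The point should be dealt with, but it does not show that the design cannot work.

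**What to change.** - **Statistical analysis:** state that the six primary violence outcomes are tested with Holm at an overall 0.05, separately from the secondary outcomes and whatever the MANCOVA shows. This keeps the chance of any false violence claim at or below 5%, whether or not a secondary outcome improves.
- **Calculation of the sample size:** state that the 80% refers to a single unadjusted contrast, give the assumed prevalence and sidedness, and add the power at the adjusted level.

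**Cost.** The change is to wording and needs no extra participants. The stated power per outcome becomes less favourable. Only if the sponsor wanted 80% at 0.05/6 for each outcome would the sample grow: 517 completers, so 1034 per arm one-sided, or 598, so 1196 per arm two-sided, at 50% v 40% and 50% dropout.

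**Optional.** Two overall primaries, victimization and perpetration, with the types as secondary, would reduce the penalty. This is not required and has drawbacks: it alters the outcomes of a prospectively registered trial, and an item total would be dominated by psychological violence (16 of the 24 items in the short inventory, against 4 physical and 4 sexual).
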